**Fig. 1 Fig1:**
[figure not shown]
Participants. Six hospitals from Japan, and 3 hospitals from Malaysia join. Juntendo Urayasu Hospital and Shimada general hospital is in one cluster due to highly comparable geographical conditions (Chiba, Japan) and the expected relatively low number of enrollments (They can enroll patients during Monday to Friday, 9 a.m. to 4.p.m.)

### Routine clinical assessment

All study patients will undergo initial clinical assessments along with completion of the case record form, which includes a physical examination, documentation of symptoms, clinical history, cardiovascular risk factors, 12-lead electrocardiography (ECG), bedside cardiac ultrasound sonography (visual ejection fraction and an evaluation of the wall motion), chest X-ray, blood pressure, heart rate, and standard blood tests. Hs-cTnT (manufactured by Roche Diagnostics, Rotkreuz, Switzerland) is routinely determined and results provided to the treating physicians as part of the local standard of care in all participating centers in both treatment groups. This hs-cTnT-assay has a 99th percentile concentration of 14 ng/L with a corresponding coefficient of variation of 10% at 13 ng/L [12]. Limit of blank and limit of detection have been determined to be 3 and 5 ng/L. The physicians will complete the modified History, Electrocardiogram, Age, Risk factors and Troponin (HEART) score and the ED Assessment of Chest pain Score (EDACS) [15–17], and the HEART score will be further modified using the hs-cTnT level [18].

### Stepped wedge design

This study has a stepped wedge design, which is a type of cluster-randomized trial. This design gives all participating general practitioners the opportunity to use the intervention during the study. The group of hospitals to which the intervention applies will be called a “cluster.” Basically, each cluster contains one hospital, except for one cluster containing two hospitals—Shimada General Hospital and Juntendo University Urayasu Hospital—which are included in one cluster due to highly comparable geographical conditions (Chiba, Japan) and the expected relatively low number of enrollments because they can enroll the patients from Monday to Friday (9 a.m. to 4 p.m.) in both centers. Therefore, this study consists of 11 clusters with 12 hospitals. At study start, all clusters will apply “usual care” (control condition) to all patients, i.e., risk assessment and subsequent management includes hs-cTnT but not the application of the 0/1-h algorithm. Every 1.5 months, one randomly allocated cluster will sequentially start to follow the 0/1-h algorithm after a transition period of 1.5 months in all chest pain patients (intervention condition; 0/1 care) (Fig. 2).

**Fig. 2 Fig2:**
[figure not shown]
Study design. This study consists of 11 clusters with 12 hospitals. At study start, all clusters will apply “usual care” (control condition) to all patients, i.e., risk assessment and subsequent management includes hs-cTnT but not the application of the 0/1-h algorithm. One randomly allocated cluster will sequentially start to follow the 0/1-h algorithm after a transition period of 1.5 months in all chest pain patients (intervention condition; 0/1 care)

### Sample size, level of significance, and power

A survey of ED physicians found the tolerable rate of missed major adverse cardiac events to be less than 1% [19]; however, an analysis by Kline et al. showed that a 2% rate of missed diagnoses of ACS might be considered acceptable considering the risk of harm from further testing [20], and more than 2% of ACS patients are inappropriately discarded annually according to a Medicare database [21]. Regional differences in the management of NSTE-ACS persist in Asian countries even after extensive adjustment for baseline characteristics and treatment [12]. Indeed, in previous studies, the MACE rates tend to be higher than in Central European or North American countries and vary from 1 to 4% [10, 18, 22, 23]. We estimated that, in the standard care arm, patients managed as outpatients by usual care would experience an event rate of 3%, for the primary outcome of MACE including all-cause death, subsequent myocardial infarction, unstable angina, or unexpected revascularization in 30 days. The non-inferiority margin of 1.5% is based on clinical judgment and the available literature, thus, accepting an upper limit of the 95% confidence interval. No assumption was made about the level of intra-cluster correlation coefficient (ICC) [24]. Based on these numbers, a one-sided significance level of 5% and a power of 80%, the required total sample size for a stepped wedge design with 11 clusters was determined to be 4260.

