### Recalculation of sample size, level of significance, and power due to outbreak of severe acute respiratory syndrome coronavirus 2(SARS-CoV2)

Due to the influence of SARS-CoV2, the recruitment of Chiba, Chiang-Mai hospital, and Taipei city hospital has been sluggish. When the sample size was redesigned about 2 months after the start of the test, the power dropped to 67%. The SARS-CoV2 situation is unpredictable and we considered the possibility of reduced recruitment in other clusters. As a result of discussions within the research group, a non-randomized facility was added as the 11th cluster (Institute Jantung Negara) to ensure power. Furthermore, we extended each duration of the step from 1.5 to 2.5 months from the 12th steps. The overall “almost” randomized study is a limitation, but as a result, the power increased to 80%.

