### Transition period: implementation support

To support the implementation of the 0/1-h algorithm during the transition period, we will provide written educational material and presentations at each site as well as training for clinical and laboratory staff. Educational material on the algorithm and decision thresholds will be presented at each ED handover (twice daily) during the transition period to ensure wide coverage of staff on all shift patterns. This will be reinforced by specialist chest pain nurses who will receive detailed training prior to implementation and who support ED clinicians in assessing patients with suspected ACS. Key details from the educational presentation will be formatted into a one-page reference guide that will be posted within each department and online in the hospital guidelines portal. This information will also be presented to the wider hospital teams in medical grand round presentations prior to implementation and circulated to all general practitioners. Laboratory staff will also receive training to ensure that any queries directed to the laboratory will be dealt with consistently. Finally, the research team will include senior cardiologists, emergency physicians, and cardiology nurses who are clinically active within each of the hospital clusters; education will therefore be reinforced at a local level by these clinical leaders throughout the transition period. This period will not be subject to an analysis.

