### Statistical analyses

Continuous variables will be presented as the mean (standard deviation) or median (interquartile range [IQR]), and categorical variables will be presented as numbers and percentages. The 30-day incidence of MACEs will be analyzed using generalized linear mixed models after adjusting for background information and seasonal effects. The clustering effect by hospital will be considered in this analysis as a random effect. The binomial distribution and identity link will be used to directly estimate the absolute differences in MACE incidence between 0/1-h algorithm care and usual care patients. The main model will include conditions (control or intervention) and steps (time periods) as categorical variables and hospitals as clusters. Differences in MACEs with a 1-sided 95% CI will be estimated in order to evaluate non-inferiority. The non-inferiority margin is preset at 1.5%. The sensitivity and negative predictive values (NPVs) for MACEs in the rule-out group and the specificity and positive predictive values (PPVs) for MACEs in the rule-in group will be calculated. Multiple imputations will be used to handle missing data. The statistical analyses will be performed using the SAS software program, version 9.4 (SAS Institute, Cary, NC, USA), and R version 4.0.3 (R Foundation for Statistical Computing, Vienna, Austria).

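### The 80% power claimed for 4260 patients is not delivered by the stepped wedge layout and step-adjusted model: with equal arms it is about 65% at zero intra-cluster correlation and lower with any small positive one

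*Protocol article*

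**What the plan says.** The section on sample size, level of significance and power gives these inputs: "a one-sided significance level of 5% and a power of 80"%, the expectation that "patients managed as outpatients by usual care would experience an event rate of 3"%, and a margin described as follows: "The non-inferiority margin of 1.5% is based on clinical judgment and the available literature". On clustering it says "No assumption was made about the level of intra-cluster correlation coefficient (ICC". It concludes that "the required total sample size for a stepped wedge design with 11 clusters was determined to be 4260". It gives no assumed event rate under the algorithm and mentions no allowance for time effects or for the transition.

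The section on recalculation after the SARS-CoV2 outbreak reports that power had fallen to 67% about two months into the trial, that "a non-randomized facility was added as the 11th cluster", that later steps were lengthened from 1.5 to 2.5 months, and that power came back to 80%.

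Three other sections determine precision. Under Stepped wedge design, one cluster switches at each step, after a transition period. The transition section says of that period: "This period will not be subject to an analysis". Under Statistical analyses, the absolute risk difference is estimated with a hospital random effect, and "The main model will include conditions (control or intervention) and steps (time periods) as categorical variables and hospitals as clusters".

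**The concern.** In a stepped wedge trial the intervention is confounded with calendar time by design: early periods are nearly all control and late periods nearly all intervention. Once steps enter the model as categories, the before-after contrast no longer counts as information about the treatment. What remains is the comparison between clusters within a period and, if cluster effects exist, a weighted combination of that with within-cluster changes net of time. Dropping the transition cells removes more information. A sample size that ignores these features will be too small for the model that produces the primary result.

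The primary analysis is a non-inferiority test on major adverse cardiac events, and the Limitations section says the study is powered for it. If the real chance of showing non-inferiority between equal arms is well below 80%, an inconclusive result is more likely than readers will assume.

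**Working it through.** **Inputs from the article.** Event rate p = 0.03, so p(1 − p) = 0.0291. Margin 0.015. One-sided 5% (z = 1.645). Target power 80% (z = 0.842). N = 4260, 11 clusters, one switch per step, one transition step per cluster excluded, categorical steps, hospital random effect, risk-difference scale.

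**Assumptions that the article does not supply.** True difference 0; equal cell sizes; a grid of 13 periods (11 switches, one transition step each); ICC varied from 0 to 0.05.

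**1. Attempt to reproduce 4260 and 80%.** An individually randomised trial needs 2 × (1.645 + 0.842)² × 2 × 0.0291 / 0.015² ≈ 3198 patients. With 4260 its power would be 89%. So 4260 is 4260/3198 = 1.33 times the individually randomised size. No stepped wedge calculation with step effects gave 4260.

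**2. ICC 0, steps in the model, no transition gap (12 periods).** With j of 11 clusters on intervention in period j (j = 0 to 11), the average within-period variance of the treatment indicator is Σ j(11 − j) / (121 × 12) = 220/1452 = 0.1515, against 0.25 for parallel randomisation. The design effect is 0.25/0.1515 = 1.65.
- SE = √(0.0291 / (4260 × 0.1515)) = 0.00671
- Power = Φ(0.015/0.00671 − 1.645) = Φ(0.59) = 72%
- N for 80% ≈ 1.65 × 3198 ≈ 5280

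**3. ICC 0, transition cells removed (13 periods, 143 − 11 = 132 analysed cells, 4260/132 = 32.3 patients each).** Periods 1 to 11 each have ten analysed clusters, k on intervention and 10 − k on control, with k running from 0 to 10. The first and last periods have only one condition and carry no information at ICC 0.
- Information = 32.3 × Σ k(10 − k)/10 = 32.3 × 16.5 ≈ 532.5
- SE = √(0.0291/532.5) = 0.00739
- Power = Φ(0.015/0.00739 − 1.645) = Φ(0.385) = 65%
- The SE needed for 80% is 0.015/2.486 = 0.00603, so N ≈ 4260 × (0.00739/0.00603)² ≈ 6400

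**4. ICC above 0.** Generalised least squares on the same 132 cells, with period effects and a cluster random effect; the half-width is 1.645 × SE.

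| ICC (assumed) | SE | One-sided 95% half-width, points | Power, steps in model | Power, steps ignored |
|---|---|---|---|---|
| 0 | 0.00739 | 1.22 | 65.0% | 89.0% |
| 0.001 | 0.00790 | 1.30 | 60.0% | 86.7% |
| 0.005 | 0.00881 | 1.45 | 52.3% | 83.0% |
| 0.01 | 0.00920 | 1.51 | 49.4% | 81.6% |
| 0.02 | 0.00947 | 1.56 | 47.6% | 80.8% |
| 0.05 | 0.00956 | 1.57 | 47.0% | 81.0% |

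In this layout 80% or more appears only in the last column, which leaves out the step effects that the main model includes.

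**5. Sensitivity.**
- If 4260 counts transition patients, about 4260 × 132/143 = 3932 are analysed: 62% at ICC 0, 47% at 0.01.
- Without a transition gap: 72% at ICC 0, 56% at 0.01.
- Grids of 12 to 15 periods, with and without late steps of 2.5 months: 55 to 68% at ICC 0, about 45 to 51% at 0.01.
- Unequal cluster sizes (coefficient of variation 0.4 to 0.8): mean 62 to 64% at ICC 0, 47 to 49% at 0.01.
- A linear time trend in place of categorical steps barely matters: 65.3% at ICC 0 on the 13-period grid.
- Binomial simulation (4224 patients after rounding): 64% at ICC 0, 48% at 0.01.

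**The case against.** **The assumed true difference is not stated.** This is the strongest counter-argument, because non-inferiority power is very sensitive to it. With a true rate of 2.65% under the algorithm, the 13-period layout at ICC 0 gives Φ((0.015 + 0.0035)/0.00739 − 1.645) = Φ(0.86) ≈ 80%. The Introduction does cite evidence that later serial retesting is less safe. So a reader should not infer that 4260 fails to reach 80% under every assumption or at every ICC; the shortfall is shown for equal arms over the range checked. However, the article nowhere says that an advantage was assumed, and equal arms is the usual planning assumption. If an advantage was used, it should be stated.

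**The ICC is the reviewer's choice.** A reader might infer that the true power is a coin toss. That needs an ICC of roughly 0.005 or more, and the article gives none. The shortfall itself does not depend on the ICC, since it is already present at 0.

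**The layout figure is not shown.** This is correct, and 65%, 49% or 6400 should not be read as exact figures for this trial. The direction held in every layout tried.

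**The cluster count.** A reader might see a contradiction between deriving 4260 for 11 clusters and adding the eleventh later. The sample size section can equally be current text updated after the redesign, with the later section recounting its history. What stands is only that the article does not say which calculation produced 4260.

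**Low power does not bias the estimate or raise the rate of false non-inferiority claims.** This is true, and the point concerns only the stated power.

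**Conclusion.** The concern holds in this form: the stated 80% for 4260 patients does not follow from the design and main model in the same article. With equal true rates of 3%, equal cell sizes and the transition excluded, power is about 65% at ICC 0, about 60% at 0.001 and about 47 to 52% for assumed ICCs of 0.005 to 0.05. The most favourable step-adjusted layout, with no transition gap and ICC 0, reaches 72%. No step-adjusted layout checked over a plausible ICC range reaches 80%.

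The conclusion rests on a zero true difference and on 4260 being the number analysed. The 3% is stated for patients managed as outpatients; if only those are analysed and 4260 counts everyone enrolled, power is lower still. The documents do not support going further and calling the trial invalid or fixing one true power figure.

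**What to change.** Replace the 80% claim in the sample size section and in the recalculation section with power computed under the model in Statistical analyses: the actual clusters, steps and step lengths, transition cells removed, observed or expected cluster sizes, categorical steps and hospital random effect. Give it over a stated ICC range, for example 0 to 0.05, with the assumed true difference written out, and report the expected one-sided 95% confidence interval half-width beside the 1.5-point margin. Say whether 4260 counts transition patients, and whether it comes from the original or the redesigned calculation. Bring the Limitations statement about power into line.

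The cost is one recalculation and a few restated sentences. No extra enrolment and no change to the margin, significance level or model is needed. The downside is a less favourable stated power.

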### Recalculation of sample size, level of significance, and power due to outbreak of severe acute respiratory syndrome coronavirus 2(SARS-CoV2)

Due to the influence of SARS-CoV2, the recruitment of Chiba, Chiang-Mai hospital, and Taipei city hospital has been sluggish. When the sample size was redesigned about 2 months after the start of the test, the power dropped to 67%. The SARS-CoV2 situation is unpredictable and we considered the possibility of reduced recruitment in other clusters. As a result of discussions within the research group, a non-randomized facility was added as the 11th cluster (Institute Jantung Negara) to ensure power. Furthermore, we extended each duration of the step from 1.5 to 2.5 months from the 12th steps. The overall “almost” randomized study is a limitation, but as a result, the power increased to 80%.

### Control condition: usual care

Based on current Asian guidelines, patients in the control condition will undergo “standard care” including hs-cTnT testing at time of ED presentation, which will be repeated 2–3 h after presentation (with further testing at the clinician’s discretion) according to respective local standard operating procedures. Patients will have their disposition determined by the treating ED clinician. Access to outpatient care will be as per local practice. Subsequent care will be physician-determined (Table 1). We are opting out of reviewing the patient data. Subjects have the right to withdraw from the study at any time for any reason.

**Table 1 Tab1:** Physician-determined care

Hospital name	Country	Biomarker	Serial measurements	Risk stratification tool and definition of low-risk	Thereshold to rule in and role out MI
Juntendo University Nerima Hospital	Japan	Roche Elecsys hs-cTnT	None	HEART score ≤ 3, depends on an attending physicians	Less than 14 ng/L
Juntendo University Urayasu Hospital	Japan	AQT90 FLEX cTnT	Depends on an attending physicians (within 6 h)	HEART score ≤ 3 or TIMI< 2; depends on an attending physicians	Less than 99th percentile
Sakakibara Heart Institute	Japan	Roche Elecsys hs-cTnT	None	None	Less than 14 ng/L
Shimada General Hospital	Japan	Roche TROP T Sensitive test	None	None	Negative
Teikyo University Hospital	Japan	Roche Elecsys hs-cTnT	3 h	None	Less than 14 ng/L
Yokohama Rosai Hospital	Japan	Roche Elecsys hs-cTnT	3 h	None	Less than 14 ng/L
NHCS and Sengkang General Hospital	Singapore	Roche Elecsys hs-cTnT	2 h	EDACS < 16; Delta Troponin rise < 5 point (depends on the attending physician)	Male ≤29 ng/L, Female ≤19 ng/L
Maharaj Nakorn Chiangmai Hospital	Thailand	Roche Elecsys hs-cTnT	Depends on an attending physicians (within 6 h)	None	Less than 14 ng/L
Taipei City Hospital Yangming Branch	Taiwan	Roche Elecsys hs-cTnT	Depends on an attending physicians (within 6 h)	None	Less than 14 ng/L
UiTM	Malaysia	Roche Elecsys hs-cTnT	Depends on an attending physicians (within 3 h)	None	Less than 14 ng/L
Kuala Lumpur Hospital	Malaysia	Roche Elecsys hs-cTnT	Depends on an attending physicians (within 3 h)	None	Less than 14 ng/L
Institute Janutng Negera	Malaysia	Roche Elecsys hs-cTnT	Depends on an attending physicians (within 3 h)	None	Less than 14 ng/L

### Intervention condition: the 0/1-h algorithm

The 0/1-h algorithm uses the blood concentrations of hs-cTnT obtained at time of ED presentation and their absolute changes within 1 h to classify patients into the rule-out, observe, or rule-in group [8]. Patients with an hs-cTnT concentration <12 ng/L at 0h and a 1hΔ <3 ng/L will be stratified into the rule-out group. In addition, a patient can be directly stratified into the rule-out group if hs-cTnT concentrations is <5 ng/L at 0h and chest pain onset was more than 3 h prior to ED presentation without the need for further serial hs-cTnT-testing. Those patients with hs-cTnT ≥52 ng/L or a 1hΔ ≥5 ng/L will be stratified into the rule-in group. The remaining patients will be placed into the observe group. Patients triaged towards rule-out may be considered for discharge from the ED after the exclusion of other life-threatening disorders causing chest pain (e.g., pulmonary embolism, aortic dissection, pneumothorax) according to the patients’ conditions and the judgment of the treating physicians. Treating physicians are free to overrule any triage recommendation of the ESC 0/1-h algorithm whenever deemed necessary. Written informed consent was obtained from all patients in this phase. Adherence of the algorithm was assessed as the percentage of patients managed without protocol violations (e.g., rule-out of NSTEMI with a single measurement [rather than 2] in early presenters, defined as patients presenting within the first 3 h after chest pain onset).

### Transition period: implementation support

To support the implementation of the 0/1-h algorithm during the transition period, we will provide written educational material and presentations at each site as well as training for clinical and laboratory staff. Educational material on the algorithm and decision thresholds will be presented at each ED handover (twice daily) during the transition period to ensure wide coverage of staff on all shift patterns. This will be reinforced by specialist chest pain nurses who will receive detailed training prior to implementation and who support ED clinicians in assessing patients with suspected ACS. Key details from the educational presentation will be formatted into a one-page reference guide that will be posted within each department and online in the hospital guidelines portal. This information will also be presented to the wider hospital teams in medical grand round presentations prior to implementation and circulated to all general practitioners. Laboratory staff will also receive training to ensure that any queries directed to the laboratory will be dealt with consistently. Finally, the research team will include senior cardiologists, emergency physicians, and cardiology nurses who are clinically active within each of the hospital clusters; education will therefore be reinforced at a local level by these clinical leaders throughout the transition period. This period will not be subject to an analysis.

### Randomization

Simple randomization will be performed. The randomization sequence of the participating clusters will be generated using computer-generated pseudo-random numbers by a statistician at the Japanese Organisation for Research and Treatment of Cancer (JORTC), who will be not otherwise involved in the study.

